### 9.4. Monitoring

All aspects of trial integrity, including data collection and storage, trial management, adverse events, and UNSW Human Research Ethics Committee compliance are overseen by a trial steering committee comprising authors [name], [name], [name], [name], and [name], along with members of the information technology and knowledge translation teams within the Black Dog Institute, and a lived-experience expert. The steering committee will meet bi-monthly over the lifespan of the trial. Potential adverse events may include undesired changes to mental health, which may or may not be related to the study. As the study does not impact routine care and is examining the effect of an evidence-based intervention for people with mild-to-moderate mental health symptoms (i.e., serious mental illness is an exclusion criteria), no serious adverse events are anticipated.

## 10. Ethics and Dissemination

### 10.1. Research Ethics Approval

The Healthy Mind study protocol and materials have been approved by Human Research Ethics Committee at UNSW, Australia (HC190393), and registered with the Australia and New Zealand Clinical Trials Register (ACTRN12620000113954). CI, [name], will communicate with the HREC, Australian and New Zealand Clinical Trials Registry, Australian Rotary Health (ARH), and any other relevant stakeholders regarding amendments to this protocol and annual progress reports.

### 10.2. Consent or Assent

Information about the study is provided on the Healthy Mind project website. Individuals can either read the information online or download a PDF. Consent is given online by clicking a checkbox at the end of the study information page after successfully completing the eligibility screen. Participants can withdraw from the study at any time for any reason by contacting the investigation team or UNSW HREC in writing. All data collected from a withdrawn participant are securely deleted from the Black Dog Institute research platform.

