## 9. Data Collection, Management, and Analysis

### 9.1. Data Collection

All self-report data are being collected electronically via standardised, self-report questionnaires that are completed via the Healthy Mind study website (described above). At each assessment point, the study website automatically issues a unique link to the study questionnaire via email. Questionnaire data are kept on a secure server at University of New South Wales (UNSW), Australia, and downloaded periodically for storage in a password-protected data file accessible by [name] and [name]

Cognitive function data are being collected electronically using CBS Health assessments administered via the CBS website (described above). All data will be encrypted during transmission to and storage on Amazon’s AWS EC2 service (OR, USA). Once stored, it will be accessible by only [name] and [name] on the password-protected platform. The only other individuals with access to the trial data are the CBS administrators, who may access the researcher account in case of a technical issue or emergency.

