### 9.3. Statistical Analysis

Statistical analyses will be performed using SPSS 25.0 (IBM Inc., Armonk, NY, USA) and MPlus (Muthen & Muthen, Los Angeles, CA, USA). Intention-to-treat analyses will be used to establish change across time and any treatment effects using linear mixed models for repeated measures (MMRM). Missing data will be handled using maximum-likelihood estimation within the MMRM procedure, as this appears to be more robust to violations of the assumption of randomness due to attrition [45]. Where appropriate, complier analyses will be used to estimate the effect of treatment-as-recommended using a complier average causal effect (CACE) procedure [46]. Cognitive sub-domain (e.g., speed of information processing) indices will be used as covariates in all analyses to determine whether cognitive profile impacts the use or efficacy of Healthy Mind. All effect sizes will be computed and reported using Cohen’s *d*.

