## 12. Limitations

Volunteer bias is a possible weakness of our study, as participants who sign up may be especially motivated to learn mental health skills and engage with an eMH program designed specifically for people with ID. Problems may occur, for example, if participation is driven by a broader commitment to improving mental health, as this is likely to enhance treatment effects. However, as Healthy Mind is intended to be freely available to all Australians in the future, recruitment of motivated individuals is likely consistent with naturalistic uptake of self-help mental health programs.

Clinical trials that include people with ID often report elevated rates of attrition where participant demand is high [38], and eMH trials also experience increased study drop-out and/or disengagement from their programs [48]. Study attrition may introduce selection effects if the remaining participants share characteristics, such as especially low or high baseline symptoms scores. Our trial protocol is relatively simple, with minimal questionnaires and measures to reduce participant burden. To reduce the impact of attrition, we will recruit a larger sample than is required on the basis of our sample-size calculation and conduct between-group analyses at baseline prior to further data analysis to confirm the preservation of randomisation. If randomisation fails, variables that demonstrate systematic differences between groups at baseline will be held constant in future analyses, where appropriate. Additionally, all trial participants will have a nominated carer assist them throughout the trial, which should improve program engagement and trial completion. To further maximise trial engagement, automated program reminders will be sent by email to carers who have partially completed or failed to complete a questionnaire.

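### Section 10.2 deletes the data of anyone who withdraws in writing, including data already collected, which conflicts with the intention-to-treat likelihood analysis in Section 9.3

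*Protocol article*

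**What the plan says.** Section 10.2 (Consent or Assent) sets out how a participant leaves the study: "Participants can withdraw from the study at any time for any reason by contacting the investigation team or UNSW HREC in writing". The next sentence gives the consequence: "All data collected from a withdrawn participant are securely deleted from the Black Dog Institute research platform". Deletion is automatic. It does not depend on a request, and it does not separate data collected before withdrawal from data that would have come later.

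Section 9.3 (Statistical Analysis) says "Intention-to-treat analyses will be used to establish change across time and any treatment effects", by a mixed model for repeated measures, and "Missing data will be handled using maximum-likelihood estimation within the MMRM procedure".

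Section 12 (Limitations) recognises the danger of losing participants: "Study attrition may introduce selection effects if the remaining participants share characteristics, such as especially low or high baseline symptoms scores". Its answers are a larger sample and a comparison of the groups at baseline, before other analyses, to check that randomisation held.

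Section 9.1 (Data Collection) describes where data are held. Questionnaire data are on a university server and are also "downloaded periodically for storage in a password-protected data file". Cognitive test data are on an external cloud service. No section says whether these copies are deleted too, or how the deletion rule fits the intention-to-treat analysis.

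**The concern.** Intention-to-treat means that everyone randomised is analysed in the allocated arm. Likelihood estimation in a repeated-measures model copes with dropout by using what each person has already contributed. A participant with a baseline and an 8-week score but no follow-up still informs the follow-up estimate. If all that person's scores are deleted, the model has nothing to use. The analysed set becomes those randomised who did not withdraw in writing, which is defined by an event after randomisation.

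Two safeguards weaken with it. Those who withdrew cannot be compared with those who stayed. The baseline comparison in Section 12 is run on survivors only, so a difference created by deletion could be mistaken for failed randomisation, and a real one could be hidden. If withdrawal depends on symptoms and differs between arms, the treatment estimate is biased in a way that a later analysis plan cannot repair from deleted data.

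**Working it through.** **1. The plan's own figure.** Section 6 needs 50 per group and allows for about 40% attrition: 100 / (1 − 0.40) = 166.7, rounded up to 167. This reproduces the recruitment target. The allowance replaces lost numbers. It does nothing about who is lost, and it does not separate written withdrawal from non-response.

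**2. The passages side by side.**
- Stops responding: no deletion. Baseline and any 8-week scores stay in the model, as Section 9.3 intends.
- Withdraws in writing: all data are deleted from the platform (Section 10.2). If Section 9.1's copies follow, nothing is left to analyse. If they do not, the plan does not say whether they may be used.

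So the conflict concerns written withdrawals only, and their number is not given.

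**3. Simple size.** Let a share p of an arm withdraw, with a mean δ worse than those who stay (mean m). The full-arm mean is (1 − p)m + p(m + δ) = m + pδ. After deletion it is m, a shift of pδ. The group difference therefore shifts by p₁δ₁ − p₀δ₀, which is zero when both arms are alike. Assume δ = 1 SD and withdrawal from one arm only:
- p = 5%: 0.05 SD, or 0.05 / 0.5 = 10% of the planned effect
- p = 10%: 0.10 SD, or 20%
- p = 20%: 0.20 SD, or 40%

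**4. Simulation.** The documents give no inputs beyond the 0.5 SD effect, so the following are assumptions: three visits with correlation 0.6 between every pair, a true difference of −0.50 SD at both later visits, and withdrawal after week 8 that is more likely with a worse week-8 score. There were 4,000 per arm and 60 repetitions. Keeping the data means that week-8 scores stay in, and follow-up is estimated by regression on baseline and week 8 within arm.

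Withdrawal from the intervention arm only:

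| Withdrawn | Kept: week 8 / follow-up | Deleted: week 8 | Deleted: follow-up | Baseline difference after deletion |
|---|---|---|---|---|
| 5% | −0.495 / −0.498 | −0.541 | −0.526 | −0.021 |
| 10% | −0.499 / −0.497 | −0.589 | −0.552 | −0.053 |
| 20% | −0.494 / −0.496 | −0.666 | −0.599 | −0.098 |

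Against −0.50, deletion moves the estimate by about 0.04, 0.09 and 0.17 SD at week 8, and by 0.03, 0.05 and 0.10 SD at follow-up.

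The same share and mechanism in both arms: deletion gives −0.495, −0.502 and −0.495 at week 8, and −0.498, −0.500 and −0.498 at follow-up. There is no bias.

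**5. A limit on these figures.** They are differences in means at each visit, the quantity Section 6 is built on. If the model's contrast is change from baseline, the artificial baseline difference is subtracted. Week 8 becomes −0.541 + 0.021 = −0.520, −0.589 + 0.053 = −0.536 and −0.666 + 0.098 = −0.568, so the shifts are 0.02, 0.04 and 0.07 SD. Follow-up becomes −0.505, −0.499 and −0.501, essentially unbiased. That last result depends on the assumed equal correlations, under which selection on week 8 moves baseline and follow-up alike.

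**The case against.** The strongest reply is that the rule is narrow and has an ethical purpose. Withdrawal takes a written notice, so most of the expected 40% attrition may be non-response, which the rule does not touch. The deletion promise belongs to a consent procedure that an ethics committee approved for people with intellectual disability. Whether to keep data after withdrawal is partly an ethical choice. All of this stands, and it limits the size of the problem. It does not remove the conflict: the article makes both promises and does not say how they fit together.

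A reader might infer more than the documents support:
- **That the data are unrecoverable.** Deletion is stated for one named platform. Section 9.1 describes other stores and is silent on them.
- **That the missingness is outcome-related.** No reason for withdrawal and no rate by arm is given. This is a plausible risk and not a stated fact.
- **That differential withdrawal follows because the trial is unblinded.** Section 8.2 says participants stay blind and that helpers in the waitlist arm do not. Whether that can hold is a separate question, and this point does not need it.
- **That allocation and adverse-event records vanish.** No section says the randomisation record is destroyed or that adverse events are held only on that platform. Section 9.4 places adverse events under the steering committee.

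**Conclusion.** The point holds in limited form. For written withdrawals, the deletion rule as stated prevents analysis as randomised and takes away the earlier scores on which the maximum-likelihood method relies. This is a stated rule that works against the planned analysis, and not a detail left to a fuller document.

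The size is unknown. The bias in the group difference is about zero if withdrawal is alike in both arms. It is roughly 0.03 to 0.2 SD, against the planned 0.5 SD, if 5% to 20% of one arm only withdraw in relation to outcome. It is smaller if the contrast is change from baseline. When worse-off participants leave the intervention arm, the bias flatters the program; when they leave the waitlist arm, it does the reverse. The withdrawal shares, the 1 SD difference, the correlation and the mechanism are all assumptions. The breach of intention-to-treat does not depend on them. The rule should be changed, but it does not by itself undermine the trial.

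**What to change.** Subject to ethics approval, and for participants consented after the change, amend Section 10.2 and the consent text along these lines: *withdrawal ends contact and further data collection; data already collected are kept in de-identified form and analysed in the allocated arm; they are deleted only if the participant explicitly asks.*

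In addition:
- Keep a non-identifying record of randomised arm and time of withdrawal, so that withdrawals and deletions can be counted and reported by arm. Where data have been deleted, those counts allow a sensitivity analysis of the pδ kind shown above.
- Reconcile Sections 9.1, 9.3 and 10.2: state whether deletion covers the university server, the downloaded file and the cloud store, and whether any surviving copy may be analysed.

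The cost is an ethics amendment and new consent wording. Section 9.1 suggests that collection was already under way, so the change helps only later enrolees. Data of those already consented must follow the promise made to them, and the arm-and-timing record for that group needs the ethics committee's agreement. The sample size does not change.

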### 10.3. Confidentiality

The eligibility screen is anonymous and no personal information is collected at this stage. Only eligible participants are asked to provide identifying information that is stored securely on UNSW servers and kept separate from other trial data in a password-protected file. Users are neither asked for nor able to enter identifying information into the Healthy Mind website itself.

### 10.4. Ancillary and Post-Trial Care

At the conclusion of the assigned waitlist period, the active intervention will be made available to all participants in the waitlist control group.

## 11. Discussion

Mental illness is 2–3 times more common in people with ID than in the general population, yet few access appropriate mental health services [4]. Electronic mental health (eMH) services are well placed to close this treatment gap by adapting cognitive behaviour therapy for people with ID, but very little is known about digital mental health care in ID.

The outcomes of this study will shed new light on how to support the mental health and psychosocial functioning of people with ID. Ours may be the first study to demonstrate the efficacy of a fully automated and self-guided eMH tool in people with ID, similar to those that benefit tens of thousands of other Australians [29]. Importantly, it may be the first time people with ID have a tool to effectively manage mood and anxiety independently [6]. Independence was an important theme in our user consultation [37] and supporting autonomy confers a range of mental health benefits to people with ID [22].

We expect our study will have practical implications for both treatment and policy. Positive results will provide confidence for ID clinicians to prescribe Healthy Mind as a digital treatment adjunct or psychoeducation tool, which is currently an unmet need in ID-specific face-to-face mental health services [13]. Results will also come as the Australian Royal Commission into Violence, Abuse, Neglect, and Exploitation of People with Disability (DRC) concludes and the Australian federal government formulates its National Digital Mental Health Framework. The DRC recently made its a finding that “people with cognitive disability have been and continue to be subject to systemic neglect in the Australian health system” [47]. Our trial will provide a clear example of how we might address this neglect with a cost-effective, scalable intervention like others widely available to people with more typical abilities [29].

## 12. Limitations

Volunteer bias is a possible weakness of our study, as participants who sign up may be especially motivated to learn mental health skills and engage with an eMH program designed specifically for people with ID. Problems may occur, for example, if participation is driven by a broader commitment to improving mental health, as this is likely to enhance treatment effects. However, as Healthy Mind is intended to be freely available to all Australians in the future, recruitment of motivated individuals is likely consistent with naturalistic uptake of self-help mental health programs.

Clinical trials that include people with ID often report elevated rates of attrition where participant demand is high [38], and eMH trials also experience increased study drop-out and/or disengagement from their programs [48]. Study attrition may introduce selection effects if the remaining participants share characteristics, such as especially low or high baseline symptoms scores. Our trial protocol is relatively simple, with minimal questionnaires and measures to reduce participant burden. To reduce the impact of attrition, we will recruit a larger sample than is required on the basis of our sample-size calculation and conduct between-group analyses at baseline prior to further data analysis to confirm the preservation of randomisation. If randomisation fails, variables that demonstrate systematic differences between groups at baseline will be held constant in future analyses, where appropriate. Additionally, all trial participants will have a nominated carer assist them throughout the trial, which should improve program engagement and trial completion. To further maximise trial engagement, automated program reminders will be sent by email to carers who have partially completed or failed to complete a questionnaire.

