#### 4.1.4. Outcomes

Outcome measures will be kept to a minimum in accordance with recommendations to reduce participant demand and minimise attrition in studies involving people with ID [38]. A summary of assessments completed online by participants at baseline, immediately post-intervention, and 3-month follow-up is presented in Table 1.

Primary outcome measures: The primary outcome measure will be the Anxiety Depression and Mood Scale (ADAMS) [39]. The ADAMS is a 28-item self-report inventory that provides an assessment of psychiatric symptoms across five domains of pathology: (1) manic–hyperactive behaviour; (2) depressed mood; (3) social avoidance; (4) general anxiety; and (5) obsessive–compulsive behaviour. As both the total ADAMS score and each of the five subfactor scores demonstrate sound validity and reliability [39], efficacy of the intervention will be defined as a significant reduction in either the depressed mood or general anxiety subfactors.

Secondary outcomes: The Kessler-10 (K10) will provide an additional assessment of psychiatric symptoms [26]. The K10 is the standard measure of general psychopathology in the Australian healthcare system and thus will allow population-level comparisons between our sample and the broader Australian community.

The World Health Organisation Disability Assessment Schedule 2.0 (WHO-DAS) will provide a measure of disability and daily functioning [40]. The WHO-DAS is a 36-item self-report measure of measure health and disability across six life domains: (1) cognition; (2) mobility; (3) self-care; (4) getting along with others; (5) daily life activities, such as domestic duties; and (6) participating in society. Domain scores will be computed using the “item–response–theory” method to enable domain-level analysis across time.

Additional measurements: The autism spectrum quotient (AQ) will provide a measure of autism spectrum disorder (ASD) symptoms previously classified in the Diagnostic and Statistical Manual of Mental Disorders (DSM-IV) as characteristic of Asperger’s syndrome [41]. ASD symptoms are common in individuals with ID and may explain treatment effects [42]. The AQ is a 50-item self-report inventory that provides an overall measure of ASD symptom severity and shows excellent discriminant validity from other psychiatric disorders [41].

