## 8. Assignment of Interventions

### 8.1. Allocation

Participants are allocated to a condition following a 1:1 allocation ratio using computerised blocked randomisation with blocks of eight. Randomisation occurs immediately after a participant completes the baseline assessment, ensuring allocation concealment.

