**Primary outcome measure**			
Anxiety Depression and Mood Scale (ADAMS)	X	X	X

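### Extra covariates enter the models only if a baseline comparison suggests randomisation failed; baseline adjustment should be fixed in advance instead

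*Protocol article*

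**What the plan says.** The rule stands in Section 12 (Limitations), where the article discusses attrition. The authors will "conduct between-group analyses at baseline prior to further data analysis to confirm the preservation of randomisation". If randomisation is judged to have failed, "variables that demonstrate systematic differences between groups at baseline will be held constant in future analyses, where appropriate". The article does not say which variables are compared, how a difference is judged, or whether the comparison covers everyone randomised or only those retained.

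Section 9.3 specifies an intention-to-treat mixed model for repeated measures with maximum likelihood. It fixes one set of covariates: "Cognitive sub-domain (e.g., speed of information processing) indices will be used as covariates in all analyses". Baseline ADAMS is not named there, although Table 1 shows that ADAMS, K10 and WHO-DAS are all measured at baseline.

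Section 8.1 describes the allocation: "Participants are allocated to a condition following a 1:1 allocation ratio using computerised blocked randomisation with blocks of eight". It adds: "Randomisation occurs immediately after a participant completes the baseline assessment, ensuring allocation concealment".

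Section 4.1.4 sets the success criterion: "efficacy of the intervention will be defined as a significant reduction in either the depressed mood or general anxiety subfactors".

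**The concern.** With concealed, computer-generated allocation, a difference between all randomised arms at baseline is a chance difference. A between-group comparison cannot show that such a process failed. What it does is select variables by the size of their chance imbalance. A covariate is useful because it predicts the outcome, and the rule takes no account of that.

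Three things follow. The primary model is not settled until baseline data have been examined, and the closing qualifier leaves the last step to the analyst. The most obvious prognostic variable, the baseline score of the outcome itself, has no guaranteed place as a covariate. And the step is offered as a protection against attrition, yet if it compares everyone randomised it carries no information about who drops out; if it is meant for retained participants, the text does not say so.

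**Working it through.** **Inputs from the article.** From Section 6: 50 per group, d = 0.5, alpha 0.025 for each primary difference, attrition of about 40%. From Section 9.3: the mixed model and the cognitive covariates.

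**Inputs assumed.** Two-sided testing; the correlation r between baseline and follow-up ADAMS (range 0.3 to 0.7); a 0.05 threshold for the baseline comparison. None is in the article.

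**The plan's own figures.** No figure is given for this rule. In Section 6, 100/(1 − 0.4) = 167 reproduces the recruitment target. The 50 per group does not follow from a two-sided alpha of 0.025, which needs 77. That is a separate matter; 50 is used here only as the planned number.

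**Step 1: how often would chance look like failure?** With k independent variables each judged at 0.05, the chance of at least one flag under perfect randomisation is 1 − 0.95^k:
- k = 5: 23%
- k = 10: 40%
- k = 15: 54%

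Any single variable, baseline ADAMS included, would be flagged about 5% of the time.

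**Step 2: what does fixed baseline adjustment gain?** Take one follow-up score with variance 1 and complete data. The residual variance is 1 if baseline is ignored, 2(1 − r) for change from baseline, and 1 − r² with baseline as covariate. The non-centrality is 0.5 × √(50/2) / √variance = 2.5 / √variance. At r = 0.5 this is 2.5 for the change score (variance 1) and 2.5/√0.75 = 2.89 for the adjusted analysis. Power from the non-central t distribution at two-sided 0.025 is 59% if baseline is ignored, and otherwise:

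| Assumed r | Change score: variance | Power | Baseline adjusted: variance | Power |
|---|---|---|---|---|
| 0.4 | 1.20 | 50% | 0.84 | 67% |
| 0.5 | 1.00 | 59% | 0.75 | 73% |
| 0.6 | 0.80 | 70% | 0.64 | 80% |
| 0.7 | 0.60 | 83% | 0.51 | 89% |

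**Step 3: what does the rule do to error and power?** This was simulated with 50,000 trials per setting, 50 per arm, one baseline and one outcome. Follow-up scores were compared, and baseline was added only if its own p-value was below 0.05:

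| Assumed r | Type I error, rule (nominal 0.025) | Power, rule | Power, always adjusted | Type I error when imbalance exceeds 0.3 SD but is not flagged |
|---|---|---|---|---|
| 0.3 | 0.0245 | 59.6% | 63.5% | 3.8% |
| 0.5 | 0.0202 | 59.7% | 72.4% | 5.1% |
| 0.7 | 0.0160 | 60.3% | 88.3% | 6.7% |

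On average the rule is conservative. Error exceeds nominal in trials with a sizeable imbalance that escapes the flag. If an analyst reported the smaller of the adjusted and unadjusted p-values, type I error would be 3.4% to 4.3% across the same r. That is a worst case, not something the article says.

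**The case against.** The strongest reply is that baseline is probably already in the model. The abstract lists baseline among three assessment times, Section 9.3 uses the mixed model to study change over time, and success is defined as a reduction. If baseline is one of the repeated measures, a group-by-time contrast takes account of it whatever the imbalance, and the exact form may be left to a fuller document. This stands against saying that baseline ADAMS is accounted for only when it looks imbalanced. It does not remove the point: with complete data and unconstrained baseline means that contrast is a change score, and Step 2 shows that it has less power than baseline adjustment at each r considered. The article specifies neither a baseline covariate nor equal baseline means.

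Other stronger readings also fail:
- A reader might infer that the rule inflates type I error. Applied mechanically it does not.
- A reader might infer that all covariates are chosen by imbalance. The cognitive indices are fixed; only additions to them are conditional.
- A reader might infer that the check certainly has no bearing on attrition. The sentence follows a remark about participants who remain, so it could mean comparing retained participants by arm, where differences need not be chance. The text does not settle this.
- The article speaks of between-group analyses, not significance tests. Tests are the natural reading, but the threshold, number and independence used in Step 1 are assumptions.

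Finally, the low absolute power in Step 2 owes much to the separate mismatch between 50 per group and alpha 0.025. The differences between columns are what bear on this rule.

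**Conclusion.** The concern holds in limited form. The article states an imbalance-triggered, discretionary rule for covariates beyond the cognitive indices, and that rule reaches the primary analysis. This is something fixed badly, not a detail left to the analysis plan. It selects covariates on the wrong ground and does not secure baseline adjustment.

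The cost is lost precision, analyst discretion, and type I error of about 4% to 7% at nominal 2.5% in trials with an unflagged imbalance above 0.3 SD. Against a change-score contrast, fixed adjustment gains 17 percentage points of power at r = 0.4, 14 at r = 0.5 and 10 at r = 0.6. These sizes rest on the assumed r, two-sided testing and complete data at a single follow-up; the error figures also assume a 0.05 flag and follow-up scores compared without baseline. The case against the rule itself does not depend on r. The change should be made, but the point does not call the validity of the trial into question.

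**What to change.** 1. Delete the imbalance-triggered rule from Section 12 and report baseline balance descriptively.
2. State in Section 9.3 that each mixed model adjusts for the baseline value of its own outcome, whatever the observed imbalance. This can be a baseline covariate with its interaction with time, or a model with baseline as a response and baseline means constrained equal across arms. For the primary outcome, use the baseline score of the ADAMS subfactor being analysed. Keep the prespecified cognitive indices.
3. For attrition, compare baseline characteristics of completers and non-completers by arm, and add baseline predictors of dropout in a sensitivity model. Section 10.2 deletes all data from participants who withdraw, so this can cover only those whose data remain; the report should say how many are missing for that reason.

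The cost is analysis wording. The baseline measures are already scheduled, and no new data collection is needed.
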